**- 16. week post operatively follow up**

TUG, 10 Meter Walking test, NMS, isometric strength both limbs.

**Secondary outcomes**
**Admission time and fall episodes**Admission time is recorded as the time from arrival at hospital to the point of time when the patient is either discharged or has died. The post-operatively day of patients meeting the discharge criteria are registered, as well as the day of prescription for a 24hour-rehabilitation unit or nursing home facilities for patients who can not be discharges to their original housing.

Training sessions during in-hospital stay and outpatient rehabilitation are recorded for both groups, including number of visits and type of training.

**Other parameters**Bodyweight and height

**Safety**The safety issue is related to strength training. Studies including strength training have not previously described safety problems, and the program planned for this study does allow an adaptation phase. Thus, based on the available evidence the patients are not exposed to any additional safety risk, other than that of possible slight muscle soreness after the first strength training sessions. The study is not blinded to the physical therapists, why the identification of possible safety issues will be easy.

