**Protocol Summary**
Elderly patients with a hip fracture are a particularly vulnerable group with high morbidity and mortality (1-3) and some patients do not regain previous level of physical function (4, 5). The most recent Cochrane review that assesses the effect of physical therapy concludes evidence from randomized trials insufficient to determine the effectiveness of different types of exercise used in the rehabilitation after hip-fracture surgery (6).

Patients with a hip fracture admitted to Hvidovre Hospital have since September 2002 been treated in the fast track concept (7, 8) in a specialized unit at the Department of Orthopedic Surgery. The treatment is optimized and intensified regarding surgery, nutrition, pain management, physical therapy, etc. during hospitalization. Despite the optimized efforts, patients who are discharged directly to their own home after following a standard course are admitted in average 16 (SD 14) days and still some patients are discharged to 24hour rehabilitation units in the primary sector. A study from the unit has shown that 32 % of patients fall again within 6 months after discharge (9). Other data collected in the unit have shown that quadriceps muscle strength of the operated limb among patients discharged directly to their own home is less than 50% of the strength of the healthy limb (10), despite the fact that they have followed an optimized treatment course.

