**Adverse events**
In this context adverse events are defined as any unintended, unfavorable finding, symptom or disease that can be connected to the strength training, whether it is deemed to have a correlation with this or not. Adverse events are recorded by spontaneous registration as well as by open questioning.

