In addition, strength exercises are already used as part of the treatment for this patient group, but not systematically as planned in this study. Patients participating in the study will, as well as the treating physicians and physical therapists, know which group they are in and they will therefore be able to respond to any issues. Patients are evaluated on a daily basis during hospitalization regarding their ability to participate in the rehabilitation and will otherwise receive treatment according the normal standards of the department. The study spans the period of hospitalization after an acute hip fracture including a 16. week post operative control. It is estimated that patients in the intervention group will experience a reduced loss of muscle strength in the operated limb, with the result that fewer people will experience new fall episodes and that more patients will recover a level of physical function as before the hip fracture. The study may prove of importance for the participants, but also further on for the many other patients with a hip fracture worldwide.
Patients are included after obtaining informed written consent from the patient himself after a minimum of 24 hours of consideration. The study is part of the "Hip fracture project" at Hvidovre Hospital and has an expected duration of 30 months. It should be emphasized that the project is not funded by the pharmaceutical industry and none of the participants have any financial or other interests in the study.

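### Admission time ends at discharge or death, so an early in-hospital death counts as a short stay; fall episodes are a named outcome with no described definition, window or collection

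*Protocol*

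**What the plan says.** The secondary outcomes stand in the protocol under the heading "Admission time and fall episodes".

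**Stay.** Admission time runs from arrival at the hospital to "the point of time when the patient is either discharged or has died". The next sentence adds a second measure: "The post-operatively day of patients meeting the discharge criteria are registered". It also registers the day on which a place in a 24-hour rehabilitation unit or nursing home is prescribed for those who cannot return to their previous housing. The Protocol Summary gives the only figure on stay: patients discharged directly home "are admitted in average 16 (SD 14) days".

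**Falls.** After the heading, the section does not return to falls. The 16-week follow-up lists "TUG, 10 Meter Walking test, NMS, isometric strength both limbs". The Adverse events section covers events "that can be connected to the strength training, whether it is deemed to have a correlation with this or not", noted when volunteered or in answer to open questions. Falls are nevertheless part of the rationale. The Protocol Summary reports that "32 % of patients fall again within 6 months after discharge", and the Lay Summary expects that in the intervention group "fewer people will experience new fall episodes".

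**The concern.** Length of stay is read in one direction: shorter is better. A rule that closes the stay at death gives the worst outcome a favourable value whenever the death comes early. A patient who dies on day 5 scores better than one who goes home on day 16. The Protocol Summary describes hip fracture patients as having high morbidity and mortality, so some in-hospital deaths are plausible. If they fell unevenly between arms, the arm with more early deaths would appear to shorten the stay.

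For falls the problem is one of data capture. Falls after discharge happen out of the hospital's sight and are largely lost unless somebody asks. A statistical analysis plan can say how falls are analysed, but it cannot supply data that no visit or form was told to collect. At stake is whether the trial can say anything about a benefit that its Lay Summary expects.

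**Working it through.** The protocol states no target difference, death rate or power for either outcome, so there is no planned figure to reproduce. The 38 per group in the Population section concerns strength and has no bearing here.

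**1. Effect of deaths on mean stay**

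Inputs from the protocol:
- 50 patients per arm (Procedures, randomized part).
- Mean stay 16 days, SD 14 (Protocol Summary). This describes only patients discharged directly home, so it is a proxy for all randomised patients.

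Assumed, because the protocol does not give them: 1 to 5 excess deaths in one arm, on day 3 to day 25.

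Shift in that arm's mean = (k / 50) × (d − 16), where k is the number of excess deaths and d the day of death.

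Standard error of the difference = 14 × √(2/50) = 2.8 days.

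| Day of death | k = 1 | k = 3 | k = 5 |
|---|---|---|---|
| 3 | −0.26 | −0.78 | −1.30 |
| 5 | −0.22 | −0.66 | −1.10 |
| 8 | −0.16 | −0.48 | −0.80 |
| 16 | 0 | 0 | 0 |
| 25 | +0.18 | +0.54 | +0.90 |

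For deaths on day 5 the shift is 0.22/2.8 = 0.08 to 1.10/2.8 = 0.39 standard errors. The largest entry, 1.30 days, is 0.46 standard errors. For scale, the difference detectable with 80% power at two-sided 0.05 is 2.8 × (1.96 + 0.84) = 7.8 days.

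**2. Where falls could be recorded**

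- Secondary outcomes: named in the heading; no definition, window, source or assessor in the text.
- 16-week follow-up: four measures, none of them falls. This list sits under the primary outcomes, so its silence on a secondary outcome is weak evidence by itself.
- Adverse events: a fall might surface through open questioning, but no question about falls is specified, and a definition tied to strength training fits the control arm poorly.
- Data registration: says that relevant data go on a form, without listing the items.

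No section describes how falls are to be collected.

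**3. What falls data could show**

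Input: 32% within 6 months (Protocol Summary), or 0.32 × 50 = 16 fallers per arm. Assuming a constant hazard, the proportion by 16 weeks is 1 − (1 − 0.32)^(16/26) = 0.211, or about 10.6 fallers per arm.

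Power to detect a halving with 50 per arm, two-sided 0.05, normal approximation for two proportions:
- 21.1% against 10.6% (16 weeks): about 30%.
- 32% against 16% (6 months): about 46%.

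A confirmatory comparison of falls is out of reach. Descriptive reporting is not.

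**The case against.** The strongest reply on stay is that the sentence is a recording rule for a hospital admission. It does not say that deaths will be analysed as discharges, and a statistical analysis plan, not shown here, may separate them. The day of meeting discharge criteria is registered as well, and death is a defined serious adverse event, so nothing needed for a sound analysis is shown to be missing. The trial population is also selected: home-dwelling, able to consent, not terminally ill. Most of this stands, and it limits the size of the point. It does not remove it, because the protocol itself fixes the end of the named outcome at discharge or death alike.

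On falls, the reply is that they are named under Registrations, that the 16-week list belongs to the primary outcomes and also omits the outpatient training that is recorded elsewhere, and that the stated purpose of the trial does not mention falls. This too stands in part.

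Some stronger readings are tempting, but the protocol does not support them:
- *Falls are never collected.* The text shows only that no collection is described. Some falls could surface through adverse event questioning.
- *Neither outcome answers its question.* Calendar stay is recorded, and a better measure is registered beside it.
- *Deaths always flatter an arm.* Only early deaths do; later ones lengthen the mean.
- *Starting the clock at arrival biases the comparison.* Time before randomisation is balanced in expectation. It adds noise, not bias.
- *A mean of 16 with SD 14 invalidates the analysis.* The normality assumption under Data processing and data analysis is attached to the primary analysis. No analysis of stay is stated.

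**Conclusion.** The point holds in a limited form. As defined, admission time lets an early in-hospital death count as a short stay. With 1 to 5 excess deaths on day 5 in an arm of 50, the shift is about 0.2 to 1.1 days against a standard error of about 2.8 days: modest, and in a misleading direction. The number and timing of deaths are assumptions, and the mean and SD are borrowed from patients discharged directly home. The case for change is that a cleaner measure is already being registered, not that the distortion would be large.

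The falls gap does not depend on these assumptions. Fall episodes are a named secondary outcome for which the protocol describes no definition, window or method of collection. Both matters concern secondary outcomes and leave the primary comparison untouched.

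**What to change.** **Stay.** Define the outcome as time from surgery to meeting the discharge criteria alive, using the postoperative day already registered. Treat in-hospital death as a competing event, compare cumulative incidence between arms stratified by fracture type (the randomisation stratum), and report deaths separately by arm. State also how patients prescribed a place in a 24-hour unit or nursing home enter the analysis; that day is already registered. Calendar stay can remain as a description of resource use.

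**Falls.** Define a fall, and state that falls in hospital and from discharge to 16 weeks are recorded in the same way in both arms, with one question at the existing 16-week visit. Report the numbers descriptively, without a confirmatory test.

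**Cost.** A few sentences in the protocol, one item on the 16-week form, a fall entry on the in-hospital form and slightly more analysis. No extra visit is needed.

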**Education**
Observations and measurements are carried out by physical therapists, doctors and nurses associated with the project.

**Adverse events**
In this context adverse events are defined as any unintended, unfavorable finding, symptom or disease that can be connected to the strength training, whether it is deemed to have a correlation with this or not. Adverse events are recorded by spontaneous registration as well as by open questioning.

**Serious adverse events**
In this context serious adverse events are defined as events or reactions that cause:
· Death
· Life-threatening situations
· Admission to hospital or prolongation of existing hospitalization
· Permanent or severe disability/incapacity
Serious adverse events must be evaluated by the investigator for possible correlations with treatment in the intervention group, to consider whether there is a reasonable possibility that the adverse event has been caused by that. The following factors are included in the evaluation:
- Consistency of time.
- Conformity with known effects of the treatment.
- Alternative reasons.
If a serious adverse event is considered to have a causal correlation with the treatment, the investigator must consider the study to be terminated ahead of time.

**Ethics**
No studies were found, dealing with intensive strength training implemented in the very early postoperative period and its importance to the rehabilitation of patients with hip fracture, why this study is so absolutely relevant, as well as it as earlier described, should not pose any safety risk to the patient. The study will be conducted in accordance with the principles of the Helsinki Declaration.
Patients are covered by Hvidovre Hospital patient insurance.
The protocol including patient information and consent forms for the randomized study is approved by the Research Ethics Committee of the Capital Region (HA-2007-0127) and registered with ClinicalTrials.gov.
The investigator is responsible for informing the Research Ethics Committee of any serious adverse event and/or major changes in the protocol. The coordinating investigator files all correspondence.

**Obtain consent**
All patients considered eligible receive oral and written information about the study. Inclusion takes place after obtaining informed consent from the patient himself. It is the responsibility of the investigator to provide patients with comprehensive written and oral information on the progress, purpose, risks and potential benefits of the study.
The project manager contacts the patient in person after admission to the Department of Orthopedic Surgery 312, Hvidovre Hospital. At recruitment, the patients should be informed that it is a scientific study, that the patient has the right to have an observer present during the information and that the patient may request a certain period for consideration after receiving the study information. To ensure that patients have at least 24 hours of consideration before signing of informed consent, the written and oral information is given as soon as possible after surgery. This, in order to provide the intervention group the possibility of beginning the strength training on the day after surgery. The oral information is provided in connection with the written information and will follow the content of this with further explanation given as needed. The oral information is adjusted according the patient's age, social affairs and education. It is ensured that the patient has understood the contents of both the oral and the written information. The project manager or another authorized person in the research group provides the oral information. The project manager shall ensure that such authorized person is thoroughly informed about the project and professionally qualified to provide the information. Consent to participate in the study is sought for on the day after providing information and after the patient has had a minimum of 24 hours for consideration on participation.

**Data processing and data analysis**

An assigned project number identifies all enrolled patients. At end of study, all personal identifiable data will be destroyed. Patients are informed orally and written, that data is stored and analyzed in a computer, the patient's anonymity will be ensured, and that the study complies with law of data protection. Assuming normally distributed data, the primary analysis will be repeated measures analysis of variance (ANOVA) to determine the systematic difference between the intervention and control group. Furthermore an intention-to-treat analysis will be carried out. The Data Inspectorate has approved the study J.no. 2007-41-1573.

**Financial disclosures**The study is part of the Hvidovre Hospital "Hip fracture project". It is emphasized that the study is not supported by the pharmaceutical industry or by any other institutions with financial interest in the studied problem, and that no participants in the project have financial or other interests in the studied problem.
Financial assistance for completion of the study will be applied for, but none of the potential sponsors in the project will have any influence or financial disclosure in the organization, implementation and interpretation of the data collected in the project.
 **Publication**The study results, both positive and negative, are planned for publication in an international English journal. The project manager prepares the manuscript, is corresponding author and is listed as the first author. All investigators are listed as authors.
Similarly, the results will be presented at national and international congresses. Provided positive experience with strength training for patients with a hip fracture, the procedure for this will be sought incorporated into national guidelines.

**Lay Summary**All patients undergoing surgery for a hip fracture has a need for rehabilitation in an attempt to regain former skills. Despite the optimization of rehabilitation during hospitalization and subsequent outpatient rehabilitation program, it has been shown that some patients are at high risk of falling again, not achieve the same level of physical function and to be long-term dependent on assistant care. Furthermore, it is shown that patients with a hip fracture, within 2 weeks after the fracture, have lost more than half of the muscular strength in the operated limb as compared to the healthy limb. Recent studies with patients who had a hip replacement, where strength training was implemented immediately after the operation as part of the rehabilitation, has shown good effect of this, but no similar studies of patients with an acute hip fracture has been found. This study will *(1)* study the feasibility of strength training (40 patients), and *(2)* by lot, randomize the 100 patients acutely admitted to Hvidovre Hospital with a hip fracture, into two groups. Patients in one group will receive rehabilitation after normal standards during hospitalization, while patients in the other group also will have to perform strengthening exercises for thigh muscles every other day during in-hospital stay. Strength exercises are performed seated, and depending on the individual strength level using with weight cuffs attached to the ankle. No side effects of strength training have been reported, apart from a possible light muscle soreness after the first sessions, corresponding to that experienced by healthy people when starting for example badminton after a summer break.

In addition, strength exercises are already used as part of the treatment for this patient group, but not systematically as planned in this study. Patients participating in the study will, as well as the treating physicians and physical therapists, know which group they are in and they will therefore be able to respond to any issues. Patients are evaluated on a daily basis during hospitalization regarding their ability to participate in the rehabilitation and will otherwise receive treatment according the normal standards of the department. The study spans the period of hospitalization after an acute hip fracture including a 16. week post operative control. It is estimated that patients in the intervention group will experience a reduced loss of muscle strength in the operated limb, with the result that fewer people will experience new fall episodes and that more patients will recover a level of physical function as before the hip fracture. The study may prove of importance for the participants, but also further on for the many other patients with a hip fracture worldwide.
Patients are included after obtaining informed written consent from the patient himself after a minimum of 24 hours of consideration. The study is part of the "Hip fracture project" at Hvidovre Hospital and has an expected duration of 30 months. It should be emphasized that the project is not funded by the pharmaceutical industry and none of the participants have any financial or other interests in the study.
